### Study design

A multi-center, three-arm, open-label randomized controlled trial will be conducted at 11 hospitals in China, including Guangdong Provincial Hospital of Traditional Chinese Medicine, the First Affiliated hospital of Sun Yat-sen University, Affiliated Hospital of Nanjing University of Traditional Chinese Medicine, the Sixth Affiliated Hospital of Sun Yat-sen University, Zhujiang Hospital of Southern Medical University, Guangdong Provincial People’s Hospital, Affiliated Cancer Hospital & Institute of Guangzhou Medical University, the First Affiliated Hospital of Guangzhou Medical University, the Fifth Affiliated Hospital of Sun Yat-Sen University, Foshan First People’s Hospital and Yuebei People’s Hospital. Participants will be recruited from the inpatient and outpatient departments of oncology and surgery. Eligible and consented patients will be randomly assigned, to receive high-dose acupuncture, low-dose acupuncture, or usual cancer with no acupuncture during the first 3 cycles of adjuvant chemotherapy after resection. Participants will be assessed at baseline and during the 3 cycles of chemotherapy (21 days for one cycle) post interventions. The design of the trial is outlined in Fig. 1.

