### Randomization

Patients will be randomly assigned to the HA group, LA group, and control group (1:1:1), using the central randomization system, allowing for full allocation concealment, provided by the Clinical Trial Management System of Xiyuan Hospital, China Academy of Chinese Medical Sciences (CACS). Random assignment will be stratified by resection extent (total/ proximal or distal gastrectomy) and neoadjuvant chemotherapy status (yes or no). An Electronic Data Capture (EDC) system provided by Xiyuan Hospital CACS will be used for research data management. The study coordinator at each site will ensure that the informed consent form has been obtained from each participant before randomization.

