### Outcomes

#### Primary outcome

The primary outcome will be the area under curve (AUC) of Functional Assessment of Cancer Therapy – Gastric(FACT-Ga) scale Trial Outcome Index (TOI) during the 3 cycles of chemotherapy.

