### Sample size

In our pilot trial, the total AUCs of FACT-Ga TOI during the 3 cycles of chemotherapy were 5402 and 4780 in the acupuncture and control groups, respectively, with a standardized derivation of 1109 [27]. Thus, a total of 62 participants will be needed in each arm to detect a significant difference between the control group and either LA or HA group, with an α of 0.025 and a power of 80%. Considering the total dropout rate of 22.41% in our pilot study and eliminating the impact of COVID-19 epidemics, we plan to enroll a total of 249 patients to allow a dropout rate of 25%.

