### Statistical analysis

Full Analysis Set (FAS): FAS will be composed of all randomized subjects according to the intention-to-treat analysis (ITT) principle, excluding those with the following criteria: (1) patients who request to withdraw from the study and provide an informed statement that he/she does not want to be analyzed, (2) patients who do not meet the inclusion/exclusion criteria incorrectly included when random, and (3) patients who are only with baseline data, without any data after chemotherapy in this trial.

Per-protocol Set (PPS): PPS will be composed of patients who complete at least 50% treatment according to the protocol which is defined as: (1) no less than 3 cycles of chemotherapy; (2) no less than 2 cycles of acupuncture treatment with no less than 50% acupuncture treatment for per cycle (i.e., no less than 4 times acupuncture in HA group and 2 times acupuncture in LA group);

FACT-Ga and mESAS scales score, demographics data, baseline clinical characteristics, the other efficacy indicators and safety indicators will be analyzed and compared in FAS. Sensitivity analysis of FACT-Ga and mESAS scales score will be used in PPS.

Numerical data are expressed as proportions, rates and frequencies. Continuous data are presented as the mean standard deviation for normal distribution, or the median and 25 ~ 75% percentile for other distributions.

We will modify our analyses to compare the outcomes in the FAS population; we will also compare the differences in the PPS population as sensitivity analysis. Missing data will be imputed using the worst observation carried forward (WOCF) method to calculate the AUC. We will use student’s t-test, analysis of variance (ANOVA) with least significant difference (LSD) for post hoc test and baseline score as covariate, χ2 test, or Fisher’s exact test to test the differences among groups. In addition, the average and the worst score of the FACT-Ga and mESAS scale during the chemotherapy will use the same statistical method. Demographics data, baseline clinical characteristics, and the other outcomes will be reported and compared using χ2 test or Fisher’s exact test. All hypothesis tests in this study are 2-sided tests, with an alpha < 0.05. Data will be analyzed using SPSS 17.0 and Stata 11.0 software.

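### The stated primary model adjusts only for the baseline score and omits hospital and the two randomisation strata, which gives up a little precision but does not affect validity

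*Protocol article*

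**What the plan says.** The Study design section says that the trial "will be conducted at 11 hospitals in China". The Randomization section describes allocation of individual patients, "using the central randomization system, allowing for full allocation concealment", and lists the strata: "Random assignment will be stratified by resection extent (total/ proximal or distal gastrectomy) and neoadjuvant chemotherapy status (yes or no"). Hospital is not among them.

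The primary outcome is the AUC of the FACT-Ga TOI over three chemotherapy cycles. The Statistical analysis section lists the tests for group differences together: a t-test, "analysis of variance (ANOVA) with least significant difference (LSD) for post hoc test and baseline score as covariate", and chi-square or Fisher's tests. The baseline score is the only covariate named. The same method is applied to the average and worst scores of both questionnaires.

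The Sample size section takes pilot AUCs that "were 5402 and 4780 in the acupuncture and control groups, respectively", "with a standardized derivation of 1109", an alpha of 0.025 and 80% power. It arrives at 62 evaluable patients per arm and 249 enrolled. It makes no mention of hospital.

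**The concern.** The outcome is patient-reported, treatment is open-label, and several influences on the scores could differ between hospitals. Two chemotherapy regimens are allowed, part of the acupuncture prescription is individualised, the acupuncturists differ, and assessors at each site may explain the questionnaires to patients. The baseline score removes only the part of a hospital difference that is already present at baseline. Differences that arise during treatment stay in the residual. Because allocation is not balanced within hospital, an arm can also by chance hold more patients from a hospital with high or low scores.

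The two stratification factors were presumably chosen because they are expected to predict outcome. A model that ignores them does not use the balance that the stratification creates.

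What is at stake is the standard error of the comparisons of each acupuncture arm with control. Hospital and both strata are known for every patient, so this precision is available without further data collection.

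**Working it through.** **Inputs.** From the Sample size section: difference 5402 − 4780 = 622, SD 1109, alpha 0.025, power 80%, 62 per arm. From the Statistical analysis section: two-sided tests. From the Study design section: 11 hospitals. Assumed, because the article does not give them: the hospital ICC (the share of AUC variance lying between hospitals), the sizes of the hospitals and, where used, the correlation between baseline and outcome.

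**1. Reproduce the plan's sample size.** By the normal formula, n = 2 × (z₀.₉₈₇₅ + z₀.₈₀)² × (1109/622)² = 2 × (2.241 + 0.842)² × 3.179 ≈ 60.4, so 61 per arm. With the noncentral t distribution the answer is 62. At 62 per arm the standard error is 1109 × √(2/62) ≈ 199, the noncentrality is 622/199 ≈ 3.12, and power is 80.2%. Dropout: 62/0.75 = 82.7, so 83 per arm and 3 × 83 = 249. The plan's figures are correct on its own inputs. Two-sided alpha 0.05 gives 50 per arm, so 0.025 is the level to use here.

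**2. Ceiling on the gain.** If all hospital variance were removed, with arms perfectly balanced within hospital, the SD would become 1109 × √(1 − ICC). Power at 62 per arm would then go from 80.2% to 81.1%, 82.4% and 84.5% at ICC 0.02, 0.05 and 0.10. In patients per arm, 62/(1 − ICC) = 63.3, 65.3 and 68.9, which is about 1, 3 and 7 extra. This is an upper bound. Arms are not balanced within hospital, and the 80.2% belongs to a t-test without the baseline score.

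**3. Simulation under the trial's own randomisation.** There were 186 evaluable patients (3 × 62), 11 hospitals of unequal assumed size, individual allocation not stratified by hospital, a total SD of 1109 and the baseline score left out. With a random hospital intercept, 4,000 runs per setting gave:

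| Assumed ICC | Power without hospital | Power with random intercept | Change (points) |
|---|---|---|---|
| 0 | 81.5% | 81.3% | −0.2 |
| 0.02 | 80.3% | 80.4% | +0.1 |
| 0.05 | 81.4% | 82.1% | +0.7 |
| 0.10 | 81.3% | 83.6% | +2.3 |
| 0.20 | 82.6% | 88.3% | +5.7 |

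The Monte Carlo standard error of one power estimate is √(0.81 × 0.19/4000) ≈ 0.6 points, so changes below about 1 point cannot be told from none.

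A separate simulation of the same model (3,000 runs) gave gains of about 0.9, 1.0 and 3.0 points at ICC 0.02, 0.05 and 0.10. A further one gave about 0, 1 to 2, and 2 to 3 points.

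**4. With the baseline score in the model.** With an assumed baseline-outcome correlation of 0.5, power was already about 91%. The gains were then about 0.2, 0.3 and 2.3 points at ICC 0.02, 0.05 and 0.10.

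**5. Random or fixed hospital term.** With hospital as a fixed factor (5,000 runs), power went from 80.8% to 78.5% at ICC 0, 81.0% to 80.4% at 0.05, 81.0% to 82.3% at 0.10 and 81.6% to 87.2% at 0.20. A fixed term therefore costs about 2 points when hospitals do not differ, whereas the random intercept costs essentially nothing.

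**6. Type I error.** Without a hospital term it was 0.020 to 0.025 against a nominal 0.025 in the 5,000-run simulation, for ICC 0 to 0.20. In the 4,000-run simulation it was 0.024 to 0.030, similar with and without the term. Omitting hospital causes no inflation.

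The gain from adding the two stratification factors was not quantified, because the article gives nothing on how strongly they predict the AUC.

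**The case against.** The strongest objection is that nothing here is invalid. Individual central randomisation makes the analysis without hospital unbiased, and leaving out an optional precision covariate is a matter of preference. Handling of centre is a usual item for a statistical analysis plan, the article is condensed, and its sentence lists tests for all outcomes at once without ruling out further terms. No ICC above zero is documented. The article describes standardisation instead: two set regimens, protocol training for acupuncturists and assessors, and training across sites.

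Much of this stands. Validity is not in question, the gain may be close to nothing, and an unseen analysis plan may already contain the terms. What does not stand is that the article is silent. It names its covariate and, separately, its strata, so a model is stated and can be improved.

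Three stronger readings are tempting, and the documents do not support them:

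- **The trial is underpowered because clustering was ignored.** If 1109 were a purely within-hospital SD, power without a hospital term would fall to 78.0% at ICC 0.05 and 75.5% at 0.10. The article does not say whether 1109 includes between-hospital variation, and if it does, the planned 80% is unaffected.
- **The full ceiling gain in step 2 can be expected.** It assumes balance within hospital, which this randomisation does not provide.
- **Hospital should have been a stratum.** Taking each existing factor as two levels, 2 × 2 × 11 = 44 cells for 249 patients is about 5.7 per cell. Leaving hospital out of the strata is defensible.

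**Conclusion.** The point holds as a minor matter of efficiency. The stated model omits hospital and both stratification factors. This gives up some precision and leaves chance hospital imbalance unadjusted.

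A reader might infer biased estimates or false-positive findings from the omission. Neither follows, because patients are randomised individually and the simulated error rate stays near its nominal level.

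The size for a random hospital intercept is a change in power of roughly 0, 0 to 1, 0 to 2 and 2 to 3 points at ICC 0, 0.02, 0.05 and 0.10. It rests on assumed ICCs and hospital sizes and on 186 evaluable patients, and it tends to be smaller once the baseline score is in the model. The sample size needs no change on this account.

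**What to change.** Before the data are analysed, state the model for the primary AUC and the secondary scores as: treatment arm, baseline score, resection extent and neoadjuvant chemotherapy status as fixed effects, and hospital as a random intercept. Leave the randomisation as it is. If the full analysis plan already specifies this, only the article's wording needs to be brought into line.

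The cost is a slightly more complex model in place of the stated ANOVA. If the hospital variance is estimated near zero, the random intercept brings little or no gain and the hospital part of the model makes almost no difference to the result. Writing the terms down in advance also removes later discretion over whether to adjust for hospital.

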According to our pilot trial, the effect of EA should persist throughout the whole phase of the intervention, rather than at any specific time point [27]. Therefore, the standardized area under curve (AUC, 21days/cycle×3 cycles), calculated by linear interpolation, will be used to reflect the repeated measures of HRQOL (FACT-Ga) and symptom burden (mESAS) during the intervention period [41, 42]. Furthermore, we hypothesized that the effect of EA will be mainly reflected on the TOI scores, which regards more with gastric cancer.

The other pre-specified outcomes include blood test indexes (concentration of circulating myeloid-derived suppressor cells, concentration of circulating Treg cells, and the number of circulating tumor cells), the incidence of treatment-emergent adverse events defined as any adverse events happened after randomization. The severity is validated using national cancer institute common terminology criteria for adverse events (NCI-CTCAE) V4.

The outcome assessments will be performed by outcome assessors at the inpatient department of each participating site. All the outcome assessors will be trained in conducting interviews and performing measurements before the study begins and will follow a standard protocol. The schedule of measurements is presented in Table 1.

**Table 1 Tab1:** Measurements to be taken at each point in the trial

Period		Screening	1st cycle	2nd cycle	3rd cycle	4-6th cycle
Timeline		D-21-0	D1-21	D1-21	D1-21	
**Enrolment**		**×**				

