**Assessment**						
HRQOL^c^	FACT-Ga^d^		**×**	**×**	**×**	
Symptoms	mESAS^e^		**×**	**×**	**×**	
AEs/SAEs^f^	NCI-CTCAE^g^ V4.0		**×**	**×**	**×**	
Blood test indexes	MDSCs^h^	**×**			**×**	
	Tregs^i^					
	CTC^j^					

^a^MPHTJP test: Measuring pain heat threshold of Jing point and presented in the online supplementary appendix

^b^LA/HA group: Low dose acupuncture/High dose acupuncture group

^c^HRQOL: Health-related quality of life

^d^FACT-Ga: Functional Assessment of Cancer Therapy – Gastric scale

^e^mESAS: Modified Edmonton Symptom Assessment Scale

^f^AEs/SAEs: Adverse events/Severe adverse events

^g^NCI-CTCAE: National cancer institute common terminology criteria for adverse events

^h^MDSCs: Myeloid-derived suppressor cells

^i^Tregs: Treg cells

^j^CTC: Circulating tumor cells

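### The analysis section assigns χ2 or Fisher's exact tests to the other outcomes, which does not fit the three blood indexes among them (two concentrations and a cell count)

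*Protocol article*

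**What the plan says.** The Outcomes section of the protocol article lists, after the primary and the seven secondary outcomes, a further group of pre-specified outcomes. It has two parts:

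- blood indexes: "concentration of circulating myeloid-derived suppressor cells, concentration of circulating Treg cells, and the number of circulating tumor cells";
- safety: "the incidence of treatment-emergent adverse events defined as any adverse events happened after randomization".

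Table 1 schedules the block headed "Blood test indexes" at screening and in the third cycle. In the text as read, the marks stand on the first row of the block; I take them to cover all three indexes.

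The Statistical analysis section first gives a general list for group differences: Student's t-test, "analysis of variance (ANOVA) with least significant difference (LSD) for post hoc test and baseline score as covariate", χ2 and Fisher's exact test. It then ties the same method to the average and worst FACT-Ga and mESAS scores. The sentence that names the remaining variables is separate: "Demographics data, baseline clinical characteristics, and the other outcomes will be reported and compared using χ2 test" or Fisher's exact test.

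**The concern.** χ2 and Fisher's exact tests compare frequencies across categories. Two concentrations and a cell count have no categories until someone chooses them, and the article states no cut-point for any of the three. An analyst who followed the sentence literally would have to choose cut-points later, and would have no term for the screening value that the schedule provides.

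At stake is the information in the immune and tumour-cell results, and an analysis choice left open that could be closed now. The same sentence covers demographics and baseline characteristics without excepting continuous ones such as age, to which χ2 does not apply either.

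**Working it through.** **1. The plan's own figure.** The sample size is not in dispute, but it supplies the number per arm used below. Inputs from the Sample size section: AUC means 5402 and 4780, SD 1109, α 0.025, power 80%, dropout 25%.

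- Difference: 5402 − 4780 = 622.
- n = 2 × (z for two-sided 0.025 + z for 80% power)² × (1109/622)². This gives 61 per arm; the version based on the t distribution gives 61.7, so 62.
- 62 / 0.75 = 82.7, so 83 per arm; 3 × 83 = 249.

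The stated 62 and 249 reproduce.

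**2. Outcome type against named test.**

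| Other outcome | Type of data | χ2 or Fisher suitable? |
|---|---|---|
| MDSC concentration | continuous | no |
| Treg concentration | continuous | no |
| Circulating tumour cell number | count | no |
| Adverse-event incidence | categorical | yes |

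The article summarises continuous data by mean and SD or by median and quartiles. That does not fit a comparison by χ2 alone.

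**3. Illustration of the loss.** Assumptions, none of them in the documents for these indexes: 62 evaluable per arm (the plan's number for the primary outcome), one pairwise comparison at two-sided 0.05, a normally distributed index, and a difference chosen so that an unadjusted comparison of means has 80% power.

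- Standardised difference: (1.960 + 0.842) × √(2/62) = 0.503.
- Split at the common median: the proportions above it are Φ(0.503/2) = 0.599 and 1 − 0.599 = 0.401.
- Power of χ2 for 0.599 against 0.401: √(2 × 0.25/62) = 0.0898 under the null and √(2 × 0.599 × 0.401/62) = 0.0880 under the alternative. Then Φ[(0.1986 − 1.960 × 0.0898)/0.0880] = Φ(0.257), or about 60%.
- By the same formula, a cut at the 75th percentile gives 53%, and at the 90th 36%.

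**4. What the screening value could add.** ANCOVA multiplies the SD by √(1 − r²), where r is the correlation between screening and cycle 3. Power is Φ[2.802/√(1 − r²) − 1.960].

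| Assumed r | Power |
|---|---|
| 0 | 80% |
| 0.3 | 84% |
| 0.5 | 90% |
| 0.7 | 98% |

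These normal-theory figures bear on MDSC and Treg, on the log scale if need be. They say nothing exact about a cell count.

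**The case against.** The strongest reply is that this is loose drafting in a condensed article. The general list includes the t-test and ANOVA with a baseline covariate, continuous data have their own summary rule, and nothing mentions categorising a concentration. Loose wording is indeed plausible. But the article links the general method to the FACT-Ga and mESAS scores and then gives the other outcomes a separate, narrower list. At best the two sentences conflict. A full analysis plan may supply model details, but the article here names an unsuitable test rather than staying silent.

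Several stronger readings are tempting and not supported:

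- **That the test is wrong for all the other outcomes.** It is not; adverse-event incidence suits it.
- **That the investigators intend to dichotomise, choose cut-points after seeing the data, or discard the screening value.** The article says none of this. Each is only a consequence of following the sentence literally.
- **That testing baseline characteristics will distort the analysis.** The only covariate named is the baseline score, and nothing makes adjustment depend on those tests. All that stands is that χ2 is the wrong tool for a continuous variable such as age.
- **That the sentence "Numerical data are expressed as proportions, rates and frequencies" shows a deeper error.** It reads as a slip for categorical data and has no analytic effect.

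It is also fair that these indexes are neither primary nor secondary outcomes, and that the trial is not powered on them.

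**Conclusion.** The point holds for the three blood indexes: the test named for them does not suit their data type, needs cut-points the article does not give, and cannot use the screening value. It holds also, as a matter of wording, for continuous baseline variables.

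The size can only be illustrated. About 20 points of power (80% to about 60%) are lost under normality, a median split, 62 evaluable per arm and a standardised difference of about 0.5. More is lost with an off-centre cut, and the forgone gain from baseline adjustment depends on a correlation that nobody has stated. A reader might take such figures as the trial's actual loss; the documents give no SD, effect or correlation for any blood index, so they cannot be read that way.

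This is a minor point. The primary analysis, the seven secondary outcomes and the total of 249 are unaffected.

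**What to change.** Reword the last test sentence of the Statistical analysis section so that:

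- χ2 and Fisher's exact tests apply to categorical variables and adverse-event incidence only;
- MDSC and Treg concentrations in cycle 3 are compared by ANCOVA with the screening value as covariate, on the log scale if skewed;
- circulating tumour cell number is compared by a count model or a rank-based method;
- continuous baseline variables such as age are not assigned to χ2.

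The cost is a change of wording. Table 1 already schedules the blood indexes at both times, so no extra visit, sample or patient is needed.

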**Methods:**

A multicenter, open-label, three-arm randomized controlled trial with 249 patients will be conducted in China. Patients will be randomly assigned, in a ratio of 1:1:1, to receive high-dose acupuncture (HA, 7 times each chemo-cycle for 3 cycles), low-dose acupuncture (LA, 3 times each chemo-cycle for 3 cycles), or no acupuncture. The acupoints prescription consisted of bilateral ST36, PC6, SP4, DU20, EX-HN3, and selected Back-*shu* points. Patients-reported Functional Assessment of Cancer Therapy-Gastric (FACT-Ga) and modified Edmonton Symptom Assessment Scale (mESAS) during the therapy will be recorded. Area under curve (AUC, 21 days/cycle × 3 cycles) and average trajectory of FACT-Ga and mESAS will be calculated. The primary outcome will be the differences in AUC of the FACT-Ga Trial Outcome Index (TOI) between HA and LA versus control groups. Secondary outcomes include AUCs and average trajectory of other FACT-Ga subscales and mESAS scores.

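### The sample size uses two-sided alpha 0.025 per acupuncture-versus-control comparison, but the analysis section sets every test at 0.05 with no stated gate or adjustment, so family-wise error control for the primary outcome is not guaranteed

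*Protocol article*

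**What the plan says.** - **Primary question.** The abstract's Methods paragraph defines the primary outcome as the difference in AUC of the FACT-Ga TOI "between HA and LA versus control groups". That is two comparisons sharing one control arm. HA versus LA is a separate second aim in the Background.
- **Sizing.** The Sample size section seeks a significant difference "between the control group and either LA or HA group, with an α of 0.025 and a power of 80" percent. It does not say whether the 0.025 is one-sided or two-sided.
- **Testing.** The Statistical analysis section says: "All hypothesis tests in this study are 2-sided tests, with an alpha < 0.05". The 0.025 level does not reappear there.
- **Methods.** The same section lists Student's t-test, "analysis of variance (ANOVA) with least significant difference (LSD) for post hoc test" with the baseline score as covariate, and tests for categorical data. It does not say which applies to the primary outcome, whether LSD is read only after a significant omnibus test, or whether p-values are adjusted.

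**The concern.** A per-comparison alpha of 0.025 with two primary comparisons looks like a Bonferroni split of 0.05. If so, the sizing assumes that the chance of at least one false primary claim is held at 5%. The analysis section then puts all tests at 0.05, which includes the primary ones, and the methods it names do not in themselves adjust pairwise p-values.

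What is at stake is the meaning of a primary result with p between 0.025 and 0.05 for one dose. Under the blanket sentence it is significant. At the level used to size the trial it is not. The trial is open-label, its outcome is patient-reported, and it is presented as confirming a pilot signal, so the rule for success should not be left open to choice once the data are seen.

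**Working it through.** **1. Which alpha was used for sizing?**

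Inputs from the Sample size section: mean AUCs "were 5402 and 4780 in the acupuncture and control groups, respectively"; SD 1109; power 80%; alpha 0.025; 62 per arm.

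Difference = 5402 − 4780 = 622. Standardised effect d = 622 / 1109 = 0.561.

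Normal approximation: n per arm = 2(z_alpha + z_power)² / d².

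- Two-sided 0.025: 2 × (2.241 + 0.842)² / 0.561² = 60.4, so 61. The t-test version gives 61.7, so **62**, with power 80.2% at 62.
- Two-sided 0.05, which is the same as one-sided 0.025: 2 × (1.960 + 0.842)² / 0.561² = 49.9, so 50. The t-test version gives 51.
- One-sided 0.05: 40 (t-test 41).
- Two-sided 0.0125: 71 (t-test 73).

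Of these, only two-sided 0.025 gives 62. With 25% dropout, 62 / 0.75 = 82.7, so 83 per arm, and 3 × 83 = 249 as stated. The 0.025 is therefore not a one-sided restatement of the two-sided 0.05 in the analysis section.

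**2. Family-wise error under each reading of the analysis text**

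Assumptions: three arms of 62, normal data, equal variances, no covariate, no true difference between arms. Simulated figures come from 400,000 trials.

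*No gate (t-tests, or LSD read regardless of the F-test), each test at two-sided 0.05.* The two control comparisons share an arm, so their statistics have correlation 0.5. The error is 1 − P(|Z1| < 1.96 and |Z2| < 1.96) = 0.0907; simulated 0.0903. For all three pairs, the studentized range with 183 degrees of freedom gives 0.1218; simulated 0.1221.

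*LSD only after a significant omnibus F-test at 0.05.* With three groups, if any two pairwise nulls are true then so is the third. The global null is therefore the only combined hypothesis, and the F-test covers it. Simulated error: 0.050 for all three pairs and 0.042 for the two control comparisons. If only HA works (d = 0.561), the false LA-versus-control rate is 0.050.

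*Two control comparisons, each at two-sided 0.025.* Error 0.0465; simulated 0.0461.

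**3. Power per comparison at 62 per arm, d = 0.561**

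- Two-sided 0.025: 80.2% (two-sample t-test).
- F-gated LSD at 0.05: about 85% (simulated 0.846).
- Ungated 0.05: 87.2%.

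**The case against.** The strongest reply is that the analysis text, read sympathetically, already controls the error. It places LSD as the post hoc step of an ANOVA. In the classical procedure that step is taken only after a significant F-test, and with exactly three groups this holds the family-wise error at 5%. For the two control comparisons it is even slightly stricter than the 0.025 split (4.2% against 4.6%). The t-test stands in a general list covering all outcomes. For a continuous outcome with three arms and a baseline covariate, ANOVA with LSD is the listed method that fits. A sample size section also gives planning inputs and not a decision rule, and sizing at a stricter level than the test is conservative for power. Finally, this is a condensed article, and an unseen analysis plan may settle the matter.

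Most of this stands, and it limits the point. A reader might infer that the plan's family-wise error is simply lost, or that it doubles. The document does not support that, because doubling needs the ungated reading and the text does not commit to it. Nor does it support the inference that the sizing section makes a p-value of, say, 0.03 a failure, since that section sets no success criterion.

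What does not fall is the conflict itself. The article states two levels for the same two comparisons. The gate can be read into the text but is not written there, and pairwise t-tests are not ruled out for the primary outcome. Even gated LSD at 0.05 is a different rule from 0.025 per comparison, so the two sections would still need to be aligned. An unseen plan could choose between them, but the published text would still contradict itself.

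**Conclusion.** The point holds as a contradiction between two sections and as missing assurance of error control. It does not show that error control has failed. The sizing rests on two-sided 0.025 per control comparison, while the analysis section applies two-sided 0.05 to everything. Depending on the reading, the chance of at least one false claim among the two control comparisons is about 9.0% (ungated) or 4.2% (F-gated). For all three pairs it is about 12% or 5.0%.

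These figures assume 62 evaluable patients per arm, normality and equal variances, and leave out the baseline covariate. Multiplicity across secondary outcomes is not counted.

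A reader might also suspect the sample size. It is not at fault: 62 per arm and 249 in total reproduce, and power is at least 80% per comparison under every rule considered, if the pilot effect and SD hold.

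**What to change.** In the Statistical analysis section, state one rule for the AUC of TOI.

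- **Preferred:** test HA versus control and LA versus control each at two-sided 0.025, as sized, with 97.5% confidence intervals, and keep HA versus LA outside the primary family.
- **Alternative:** analyse by ANCOVA with the baseline score, and read LSD comparisons at two-sided 0.05 only if the omnibus F-test is significant at 0.05. HA versus LA may then sit within the gated procedure. Add to the Sample size section that sizing at 0.025 was conservative.

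Under either rule, exclude unadjusted t-tests for the primary outcome and limit the blanket 0.05 sentence to the other outcomes.

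The cost is a few sentences, settled before the data are analysed, and enrolment stays at 249. Under the 0.025 split, a comparison with p between 0.025 and 0.05 can no longer be called positive, and power is 80% rather than about 85% with the gated procedure. Under gated LSD such a comparison can still be positive, provided the F-test is significant.
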